**Figure 3 fig3:**
[figure not shown]
Study design and sample structure of the multi-level FRESH study.

### Development of the FRESH intervention

The FRESH Intervention Working Group will develop the FRESH intervention based on our previous experiences, the results of our formative research, and the input of the FRESH Community Advisory Boards (CABs). Two CABs will be formed, one for Baltimore and one for the DC metro area. CABs will help us stay grounded in community insights by helping us engage with individuals and organizations to maximize the impact of our project, increase project sustainability, and broaden the acceptance of our efforts with communities. Each CAB will be comprised largely of community members, particularly neighborhood association members and restaurant owners, as well as policymakers and food advocacy stakeholders. Members of the CABs will attend CAB meetings to provide feedback on: (1) eligibility of study neighborhoods, (2) identification of restaurants eligible for intervention in neighborhoods, (3) engagement and recruitment strategies, (4) design of data collection tools, (5) design of intervention strategies and materials, (6) how to manage implementation challenges, (7) the group model-building and simulation modeling components, and (8) how best to disseminate and support community initiatives that help improve project sustainability. CAB meetings will be ongoing for the duration of the project. CAB members will determine the frequency of meeting times based on the need to share study milestones and challenges, and when the study team would most benefit from CAB feedback. FRESH CAB members receive a $100 honorarium for their time sharing their input and insights.

### The FRESH intervention

The FRESH intervention will be delivered by three to four trained interventionists over a 12-month period in three phases, each lasting approximately 4 months (Table 2): Engagement, Lower sugar beverages and Healthier meals. Each phase will include activities at the restaurant, consumer and supplier levels. Interventionists will share lived experiences similar to that of individuals working in the independently-owned restaurant businesses (e.g., having owned a restaurant before; working in sales; having a food/nutrition background or interest in restaurants) to prioritize the interventionists’ ability to build rapport with restaurant owners, which will be crucial to obtaining restaurant owner’s buy-in and follow-through on the intervention.

**Table 2 tab2:** Overview of FRESH intervention strategies.

Phase of FRESH	Restaurant-level	Consumer-level	Supplier-level
Engagement	Menu changes discussion; preparation of new menu formats (menu board, laminated, QR code, etc.)	Digital marketing selection (social media platform, influencer engagement, website, online delivery, etc.) Digital media to promote restaurant in general Select print media (e.g., table tents)	Initial subsidies to engage restaurants provided in the form of credit at supplier(s) used
Reduced/no sugar beverages	Offer 3 new low/no sugar beverages	Digital media to promote new beverages Print media to promote new beverages	Supplier credit to support costs of offering healthier beverages
Healthy meals	Offer 3 new healthy meals	Social media to promote new meals Print media to promote new meals	Supplier credit to support costs of offering healthier meals

#### Phase 1 (engagement)

This phase is intended to build rapport and trust between restaurant owners, their workers and FRESH team members (FRESH Partners). In a series of planning meetings, FRESH interventionists will meet with each restaurant owner and collectively decide on the best strategies for implementing the FRESH intervention that will be uniquely suited to that restaurant. Discussions will center around identifying three new low-sugar beverages, and three new healthier meals to be offered by the restaurant. These new items will be in addition to any existing healthy choices. A team of Registered Dietitian Nutritionists (RDNs) and graduate-level dietetic students will complete a menu analysis for each restaurant. Menu analysts will work closely with interventionists to identify potential strategies for developing healthier menu items tailored to each restaurant. Specific strategies will be selected on a case-by-case basis by the FRESH Partners and may include collaboratively introducing new recipes or replacing, reducing, or rewriting existing recipes and adjusting cooking techniques toward healthier preparation methods (e.g., baking instead of deep frying). Changes to portion size will also be considered. Based on our formative research, restaurants already have experience using healthier preparation methods, even if these methods are not used for most menu items. Therefore, it was determined that providing restaurant staff with training on healthful cooking methods was unnecessary for the intervention. At the same time, the FRESH Partners will collectively decide on how to revise the restaurant’s menus to highlight and promote these new items (and other healthier items). This may involve professional production of a new menu board, preparation of laminated menus, and/or creation of menu QR code. Discussions during this phase will also cover selection of appropriate digital and print media to promote the restaurant in general. Possible digital media will include a series of social media posts (e.g., on the FRESH Instagram account, by a local influencer), development of a restaurant website (if they do not have one), or updating of their current website. Finally, a small initial subsidy ($500) will be provided to each restaurant to support the purchase of beverages/meal items to consider for promotion, from their local supplier. All costs will be covered by the FRESH project.

#### Phase 2 (reduced/no sugar beverages)

This phase will emphasize the stocking and promotion of three healthier beverages, that are low in added sugar (<5 g/serving) and priced at or below the cost of comparable beverages. Digital and print media will be used to promote beverages identified in Phase 1 to restaurant customers. Intervention restaurants will receive incentives in the form of supplier credit ($750/restaurant) to help offset the risk of stocking these beverages during the promotional period. This incentive will be received after the beverages have been stocked. Lists of targeted beverages will be provided to suppliers to ensure there are sufficient stocks.

#### Phase 3 (healthy meals)

This phase will emphasize the restaurant offering three new healthier meal options, that optimize dietary quality and taste following the DGA (35). A healthier meal is defined as 1 lean protein; AND 1 non-starchy vegetable; AND 1 vegetable (starchy or non-starchy) OR Fruit OR whole grain OR legumes. All components must be non-fried. As with beverages, entrees meeting FRESH criteria should be priced at or below the cost of comparable items. Existing menu items may be modified to meet FRESH criteria by simply adding a new side dish to an existing entrée. Specifically, a restaurant might already sell baked chicken that comes with two side dishes. If the restaurant already offers one side dish meeting FRESH criteria (e.g., collard greens), then the restaurant could develop one additional side dish, such as black-eyed peas, and create a menu item consisting of baked chicken, collard greens, and black-eyed peas to meet FRESH criteria. Digital and print media will be used to promote the three new healthy meals identified in Phase 1 to restaurant customers. Intervention restaurants will receive incentives in the form of supplier credit ($1,500/restaurant) to help offset the risk of providing these meals during the promotional period. This incentive will be received after the three new meals have begun to be sold by the restaurant.

In addition to supplier incentives described above, FRESH intervention staff will support restaurant owners/managers in sourcing the appropriate ingredients for proper FRESH implementation and will work directly with restaurant suppliers to allow them to anticipate stocking needs, a strategy we have used successfully in the past (36, 37). Lists of targeted meal ingredients will be provided to suppliers to ensure there are sufficient stocks.

#### Achieving sufficient intensity during implementation

A key challenge will be to ensure that the FRESH intervention is implemented with sufficient intensity to lead to changes in customer dietary quality. Two strategies will be used to ensure this outcome: (1) all participating restaurants will be required to meet specific minimal standards (e.g., the introduction of at least three low-or no-calorie beverages, and at least three healthy meals); and (2) the FRESH interventionists will meet with owners/managers at least once every 1–2 months to review progress and revise strategies as needed.

#### Process evaluation

We will assess reach, dose delivered, and fidelity (38) of implementation of the FRESH intervention (36). Process evaluation forms will be filled out on REDCap (Research Electronic Data Capture) (39, 40) periodically (e.g., weekly and monthly, depending on the phase of intervention implementation) by interventionists during their regular visits to the restaurants via pre-designed checklist/observation forms and activity logs. Data will be used to calculate indicators for fidelity (e.g., the percent of owners who agree or strongly agree with the beverage stocking option, the percent of items actually stocked), reach (e.g., the percent of customers who recall seeing a promotion, the percent of cook staff trained), and dose delivered (e.g., the number of promotions delivered, the number of training sessions delivered). For each FRESH intervention component, we will divide the resulting process data into tertiles according to low, moderate, or high implementation of each component. We will aim to achieve 100% for all process measure indicators while recognizing that high standards will vary somewhat between restaurants and possibly neighborhoods, and this variation will reflect recommendations for the system dynamics model. Process data for each component of FRESH will eventually be used to calibrate the system dynamics model to guide the intensity of the delivery of future FRESH interventions via machine learning that will be able to assess the ultimate impact of the intervention on final outcomes based on implementation intensity (Phase 4).

#### Impact assessment

Our primary study hypothesis is that regular customers of participating restaurants in FRESH intervention neighborhoods will demonstrate at least a five-point increase in dietary quality as assessed by the Healthy Eating Index 2015 (HEI) score, compared to restaurant customers living in FRESH comparison neighborhoods. We will assess this primary outcome in our consumer sample, as well as a variety of additional secondary outcome measures at the consumer, restaurant and supplier levels. All recruitment materials, consent forms and data collection instruments will be in English and Spanish. The language used will depend on the preferences of the respondent.

#### Selection and training of the evaluation team

Each site will staff a measurement and evaluation team composed of three to four members, separate from the intervention team. The evaluation team will be trained over a three to five-day period prior to collecting survey and anthropometric data to achieve acceptable (>0.90) interrater reliability. Data collectors will be blinded to the treatment group to mitigate risk of bias.

#### Recruitment of the restaurant sample

Forty-eight restaurants will be recruited at baseline according to the specified inclusion criteria. The baseline data collection team will approach the owners/managers of eligible restaurants at their business using a recruitment script that describes the intervention and presents the eligibility criteria.

#### Recruitment of the customer evaluation sample

In each sampled restaurant at baseline, all present customers will be approached by the evaluation team as they exit the restaurant, and, if willing, will be screened for eligibility. The evaluation team will set up a separate time to consent potential customer participants and to collect the survey and anthropometric data at a location convenient for the customer as we have done in other studies (20, 41). The evaluation team will continue to recruit and consent participants on a rolling basis until we have complete data from 12 customers for each participating restaurant (*n* = 576). The names and contact information of all consented participants will be recorded in order to follow them prospectively to conduct the same measures at the end of the intervention (12 months prospectively).

#### Potential for restaurant and customer drop out

It is important to recognize the possibility of low engagement and inadequate participation from restaurants owners, staff, and managers, increasing our risk for low recruitment and restaurant drop out as well as customer drop out. We lean on the experience of our team in working with restaurants and intervention trials in the past and we will employ participatory research approaches (e.g., establishing a CAB per site) as well as relying on support and commitment from community organizations, restaurant suppliers, and Departments of Health to support successful engagement of and transparent communication with independently-owned restaurants. In addition, we have allowed for loss of one restaurant in each neighborhood in our power calculation by having a power of greater than 80% if there are two restaurants. Similarly, anticipating customer drop out, we have oversampled our restaurant customer sample by 20% given experiences in previous trials.

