### Sample size and power

Our power calculations are based on the primary hypothesis, which involves testing the change in mean Healthy Eating Index (HEI) of customers between study groups. Our chosen effect measure is the standardized mean effect of the intervention, representing the difference in mean change in HEI score between the intervention and comparison groups. This measure is standardized by the total variability in the outcome, denoted as the standardized main effect (ES).

$$\begin{array}{l} \mathrm{The standardized main effect}\;\left(ES\right)\\ \;=\frac{\mu_{I}-\mu_{C}}{\sqrt{\tau_{\mathrm{restaurent}}+\tau_{\mathrm{neighborhoods}}+\sigma^{2}}} \end{array}$$

Here, μ_I-μ_C is the mean difference of intervention and comparison groups, respectively. *σ*^2 corresponds to within cluster variation, τ_restaurant corresponds to between restaurant variation within neighborhoods, and τ_neighborhoods corresponds to between neighborhood variation within a site. For our calculations, we assumed a difference in means of 5 points in HEI score would be meaningful, leading to μI − μC = 5. Using data from one of our prior multilevel intervention studies (48), we estimated the standard deviation of the change in HEI outcome to be 9–10 points, giving us σ^^2^ = 9.52^^2^ ≈ 90. We also assumed the variance of change in HEI score between restaurants within a neighborhood, and between neighborhoods within a site, would be small relative to the variance within a restaurant, therefore assuming τ_restaurant = τ_neighborhood≈5_._ Thus, we aimed to be powered to detect an effect size of ES = 0.5. This is equivalent to detecting a medium-sized effect.

Power calculations were conducted using the Optimal Design program (49) and following the documentation for “Multisite cluster randomized trials with treatment at level 3 randomization” section. For all calculations, we assumed a significance level of *α* = 0.05, an effect size of *δ* = 0.5, a total of L = 2 sites (for Baltimore and DC metro area), and an effect size variability of 0, corresponding to fixed effects by site rather than random effects by site.

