We varied the number of neighborhoods per site (*K* = 4 to 12), the number of restaurants per neighborhood (*J* = 2,3,4), and the number of customers per restaurant (*n* = 10 to 20). We varied the proportion of variability in the outcome explained by site (Baltimore vs. DC metro area) from 0 to 20% (*B* = 0, 0.1, 0.2). We varied the intra-class correlation coefficients for both the level 2 variable (restaurants) and the level 3 variable (neighborhoods) from 0.01 to 0.1 (ρπ = ρβ = 0.01, 0.05, 0.1). Finally, we assumed a loss to follow-up of 20%. Power is calculated as a function of the number of neighborhoods per site, the number of restaurants per neighborhood, and the number of participating customers per restaurant at initial and follow-up visits. If 8 neighborhoods are randomly assigned to intervention and comparison groups at each site (8 neighborhoods per arm total), the power to detect an effect size a difference of 5 HEI points will exceed 80% if we recruit at least 12 customers per restaurant (*N* = 576) when ICC = 0.05. These calculations account for a potential 20% loss to follow-up.

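### The assurance of more than 80% power with two restaurants per neighborhood is not reproduced: the inputs behind the headline power give about 75% to 78%

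*Protocol article*

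**What the plan says.** Two places in the protocol article give a power figure.

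- **Sample size and power** gives the headline. With 8 neighborhoods per site, power "will exceed 80% if we recruit at least 12 customers per restaurant" (576 customers in all) at ICC 0.05, after allowing for 20% loss to follow-up. 576 customers is 16 neighborhoods × 3 restaurants × 12 customers, so this is the three-restaurant case.
- **Potential for restaurant and customer drop out** gives the contingency. The loss of one restaurant in every neighborhood is said to be covered "by having a power of greater than 80% if there are two restaurants". No ICC, B or customer loss is attached. The next sentence deals with customer drop-out through 20% oversampling.

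The inputs are in the sample size section: "we aimed to be powered to detect an effect size of ES = 0.5", "we assumed a significance level of *α* = 0.05", and between-cluster variances set by "therefore assuming τ_restaurant = τ_neighborhood≈5" beside a within-cluster variance of about 90. The design is given as "a total of L = 2 sites (for Baltimore and DC metro area), and an effect size variability of 0". B was varied over 0, 0.1 and 0.2, and the ICCs over 0.01, 0.05 and 0.1. Two restaurants per neighborhood was one of the settings examined.

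On follow-up, the customer recruitment section says: "The names and contact information of all consented participants will be recorded in order to follow them prospectively".

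**The concern.** Going from three restaurants to two removes a third of the restaurants and a third of the customers from each neighborhood mean. A design that clears 80% by only a few points with three restaurants may not clear it with two. The contingency nevertheless carries the same threshold as the headline.

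The article names restaurant drop-out as a real risk and offers this figure as protection against it. If the figure does not hold at the ICC used for the headline, readers and the funder are relying on a margin that is not there.

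**Working it through.** **Inputs** (all from Sample size and power unless noted)

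- Effect: 5 / √(5 + 5 + 90) = 0.5
- ICC: 5/100 = 0.05 for restaurants (ρ_r) and 0.05 for neighborhoods (ρ_n)
- Sites L = 2 with fixed effects; neighborhoods per site K = 8, so LK = 16
- Restaurants per neighborhood: J = 3 as planned, J = 2 after the loss
- Customers per restaurant: 12 recruited; with 20% loss, n = 12 × 0.8 = 9.6
- B = 0, 0.1, 0.2; the article does not say which value lies behind either power statement
- α = 0.05, taken as two-sided (an assumption; sidedness is not stated)

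**Formula.** For a multisite cluster-randomised trial with treatment at level 3, the design named in the article, with B taken off the neighborhood variance:

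V = ρ_n(1 − B) + ρ_r/J + (1 − ρ_n − ρ_r)/(J·n)

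λ = LK × ES² / (4V) = 16 × 0.25 / (4V) = 1/V

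Power = P[F(1, 12; λ) > 4.747], with L(K − 2) = 12 denominator degrees of freedom.

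**Step 1: the headline, J = 3, n = 9.6**

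- B = 0: V = 0.05 + 0.01667 + 0.03125 = 0.09792, λ = 10.21, power 83.4%
- B = 0.2: V = 0.04 + 0.01667 + 0.03125 = 0.08792, λ = 11.37, power 87.1%

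This agrees with the article's claim of more than 80%, so method and inputs fit its own main figure.

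**Step 2: the contingency, J = 2**

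| B | n = 9.6 (20% loss): V, λ, power | n = 12 (no loss): V, λ, power |
|---|---|---|
| 0 | 0.12188, 8.21, **74.9%** | 0.11250, 8.89, **78.1%** |
| 0.1 | 0.11688, 8.56, **76.6%** | 0.10750, 9.30, **79.9%** |
| 0.2 | 0.11188, 8.94, **78.4%** | 0.10250, 9.76, **81.8%** |

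**Step 3: checks**

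- Simulating neighborhood means at B = 0 gave 83.2% (J = 3, n = 9.6), 75.2% (J = 2, n = 9.6) and 78.3% (J = 2, n = 12).
- With 13 or 14 degrees of freedom, J = 2 and n = 9.6 give 75.4% to 79.4% over the range of B.
- Reading the 20% oversampling as 12/1.2 = 10 analysed customers gives 75.5% to 79.0%.

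**Step 4: what would bring J = 2 with 20% loss above 80%**

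- An ICC at both levels of at most about 0.040 (B = 0) or 0.046 (B = 0.2); at ICC 0.01 and B = 0, power is 94.6%.
- A total ICC of 0.05 split equally over the two levels: 87.5%.
- B = 0.2 taken off the total variance rather than the neighborhood variance: 83.6%.
- A normal approximation: 81.7% to 84.8%.
- A one-sided test: 85.4% to 87.9%.
- A total SD of 9 rather than 10: 83.2% at B = 0.

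Each of these changes an input or the method from that used in Step 1.

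**The case against.** The strongest reply is that the contingency sentence states no inputs, so it cannot be shown to be false. Some settings the article examined do exceed 80% with two restaurants: ICC 0.01, or ICC 0.05 with B = 0.2 and no customer loss (81.8%). Restaurant loss and customer loss also appear in separate sentences, so the authors may have considered restaurant loss alone. This stands as far as it goes. The origin of the figure is unknown, and a flat 75% would be unfair because it is only the B = 0 end of the range. It does not rescue the sentence as printed. The article's own variances imply ICC 0.05 at both levels, the headline uses ICC 0.05 with 20% loss, and on that basis no examined value of B reaches 80%.

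A reader might also infer that customers of a withdrawn restaurant will be dropped, and that this would bias the comparison upward by removing the least engaged intervention restaurants. The article does not support that. The sentence is a power contingency and sets no rule on who is analysed. Nothing says such customers are excluded, and the recruitment section plans follow-up of everyone who consents. No drop-out figures by arm are given, so differential withdrawal is conjecture.

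If those customers are kept, the two-restaurant case no longer describes the analysis, because the number analysed stays at three restaurants per neighborhood. That does not restore 83% power, since customers of a withdrawn intervention restaurant may lose much of their exposure. As an illustration only: if one third of intervention customers had no effect, the standardized effect would be 0.5 × 2/3 = 0.333 and power with J = 3 and n = 9.6 would be about 50% (B = 0) to 54% (B = 0.2).

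**Conclusion.** The point holds as a misstated power figure of modest size. At the inputs behind the headline, two restaurants per neighborhood give about 75% to 78% power with 20% customer loss, a shortfall from 80% of roughly 2 to 5 points. With no customer loss the range is 78% to 82%, which passes 80% clearly only at B = 0.2. The planned three-restaurant design is sound on the same inputs, at 83% to 87%.

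This rests on a two-sided 5% test, ICC 0.05 at each of the two levels, B acting on the neighborhood variance, and 12 degrees of freedom. The document does not support a stronger charge, either that the figure is wrong under every setting examined or that the plan discards customers of withdrawn restaurants.

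**What to change.** In Potential for restaurant and customer drop out, replace the claim of more than 80% with: about 75% to 78% at ICC 0.05 with 20% customer loss (78% to 82% with no customer loss), depending on the share of variability explained by site. Name the ICC, B and loss used. If the authors' figure came from other inputs, those should be stated beside it.

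As a clarification only, confirm that customers of a withdrawn restaurant are followed as the recruitment section plans and analysed in their randomised arm. Add that the number analysed then stays at three restaurants per neighborhood, but that power for a 5-point effect falls to the extent that those customers' exposure is diluted. The 83% figure should not be promised for that case.

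The cost is a few words and a slightly less favourable power figure. Enrolment, randomisation, the outcome and the primary model do not change.
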